### Implementation outcomes

*Feasibility* is the extent to which the CPAP/O2 helmet solution for non-invasive ventilation can be successfully used within the Nigeria setting. We will employ mixed methods to measure feasibility from the patient and provider perspectives using in-depth-interviews (providers), structured case report forms assessing the fit/comfort of the helmet/CPAP device (patients), and any oxygen supply issues (for each case). We will also use the Feasibility of Intervention Measure (FIM), a 4-item instrument with a 5-point ordinal scale “completely disagree” to “completely agree” that takes less than 5 min to complete [19].*Adaptability* of the strategy for implementing the use of a CPAP/O2 helmet solution for non-invasive ventilation will be measured using a qualitative research approach, with focus on assessing the process of change, what providers want to change (ideal), what they need to have changed (essential), and what is adapted in the end (reality).*Acceptability* is the perception among implementation stakeholders that the CPAP/O_2_ helmet solution for non-invasive management of COVID-19 is agreeable, palatable, or satisfactory to patients and providers. We will assess acceptability of the use of the CPAP/O_2_ helmet solution from the patient and provider perspectives using in-depth-interviews (providers), structured case report forms assessing the fit/comfort of the helmet/CPAP device (patients), and any oxygen supply issues (for each case). We will also administer the Acceptability of Intervention Measure (AIM) to providers [19]. The instrument includes four items with a 5-point ordinal scale that ranges from “completely disagree” to “completely agree,”—higher scores indicate greater acceptability.

### Data analysis

#### Qualitative data analysis

Data collected will be transcribed verbatim after the interviews [20]. Data from the interviews will be transcribed and coded using open coding to develop an initial codebook by the qualitative research team. The codebook will include a list of question prompts, initial codes, and code meanings. Adopting Braun and Clarke’s six steps approach, codes will be reviewed, compared, analyzed, and sorted into categories to reflect consistent and overarching themes [21]. The team will develop a coding tree to derive themes until thematic saturation is attained [20–23].

#### Quantitative data analysis

Both the retrospective and nested prospective case-control studies will compare differences in exposures and risk factors observed between cases and controls using Chi-square or Fisher’s exact test. All tests will use 2-tailed probability, with *P* values < 0.05 considered statistically significant. Variables that are statistically significant will be included in forward logistic regression analysis to arrive at independent measures of association.

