## Methods

### Study setting

The study will be conducted in eight COVID-19 treatment and isolation centers in Nigeria. The sites were selected based on availability of COVID-19 treatment services, geographic spread and patient volume. The eight sites are as follows: Aminu Kano Teaching Hospital; Delta State University Teaching Hospital; Federal Medical Centre, Abeokuta; Federal Medical Centre, Ebute Metta, Lagos; Lagos University Teaching Hospital; University College Hospital, Ibadan; University of Nigeria Teaching Hospital; and Alex Ekwueme Federal University Teaching Hospital.

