### Is the use of the CPAP/oxygen helmet associated with a greater risk of COVID-19 infection among healthcare workers? (specific aim 4 b)

Healthcare personnel are at increased risk of acquiring COVID-19 infection [18]. Studies of other respiratory pathogens have documented increased transmission risk associated with aerosol generating procedures (AGP), many of which can generate both large droplets and small particle aerosols. Non-invasive ventilation is considered an AGP, but it is postulated that helmet ventilation may be associated with less risk of transmission of respiratory pathogens via aerosolization given containment in the helmet and negligible air dispersion.

A case-control study design will be implemented. We will enroll clinical and environmental hospital staff who have exposure to SARS-CoV-2 via provision of direct patient care or environmental care at the eight CircumVent study sites. Consenting and eligible health care workers will complete baseline testing for SARS-CoV-2-specific antibodies and complete an exposure assessment form summarizing risk factors and potential COVID-19 exposures in the prior 1 month. All healthcare workers assessed at time 0 comprise the retrospective study cohort. Individuals who test negative for COVID-19 antibodies at time 0 will be invited to participate in the prospective study. They will be followed for up to 6 months during which they will complete monthly encounter forms to assess community and healthcare-related exposures and to document any PCR-confirmed diagnoses of SARS-CoV-2 infection. However, the study will be censored and exit interview and a second sample for SARS-CoV-2 antibodies will be obtained if and when COVID-19 vaccine becomes available at the designated COVID-19 treatment centers.

In the retrospective study, a case is defined by seropositivity to SARS-CoV-2-specific antibodies, and a control is defined by seronegativity to SARS-CoV-2-specific antibodies. In the prospective study, a case is defined by seropositivity to SARS-CoV-2-specific antibodies, or a clinical case of SARS-CoV-2 infection confirmed by PCR testing, and a control is defined by the absence of infection, either by SARS-CoV-2 PCR or SARS-CoV2 specific antibodies.

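### The infection-risk screen has no site stratum or forced site term, so if infection and helmet use both vary between the eight centres it can create or hide a helmet association

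*Protocol article*

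**What the plan says.** Under Study setting, the protocol article states that "The study will be conducted in eight COVID-19 treatment and isolation centers in Nigeria" and that "The sites were selected based on availability of COVID-19 treatment services, geographic spread and patient volume". For specific aim 4b it adopts a case-control design and says "We will enroll clinical and environmental hospital staff who have exposure to SARS-CoV-2 via provision of direct patient care or environmental care" at all the study sites. No matching by site is described. In the retrospective part "a case is defined by seropositivity to SARS-CoV-2-specific antibodies, and a control is defined by seronegativity to SARS-CoV-2-specific antibodies".

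The section Quantitative data analysis gives the analysis: "Both the retrospective and nested prospective case-control studies will compare differences in exposures and risk factors". The tests are chi-square or Fisher's exact, two-tailed, with P "values < 0.05 considered statistically significant". The variables that reach significance are then entered in a forward logistic regression, which supplies the independent associations. Site is not mentioned as a stratum, a covariate or a cluster.

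**The concern.** Aim 4b asks whether helmet use raises the risk of infection in staff. This two-step rule is the only analysis the article states for it.

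A worker's centre can affect both the background chance of being seropositive and the chance of having worked with a helmet. If both vary by centre, a pooled two-by-two table mixes the site difference with the helmet effect. Two errors can follow:

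- **False association.** If helmets are used more where infection is higher, the pooled table shows a helmet effect that exists in no centre.
- **Masked effect.** If helmets are used more where infection is lower, a real increase in risk is diluted. Helmet use may then fail the screen and never enter the regression. For a safety question this is the worse error.

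The masked effect follows from the rule as written. Whether a variable may enter the model depends on an unadjusted P value.

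**Working it through.** **Inputs from the article.** Eight sites; chi-square or Fisher's exact test; two-sided 0.05; entry to the regression only if significant.

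**Inputs assumed.** The article gives no sample size, seroprevalence or helmet use by site. I take equal sites of 25, 50 or 100 workers (N = 200, 400, 800), mean infection 25% and mean helmet use 50%, with site rates equally spaced over the ranges shown. The simulations compare an uncorrected Pearson chi-square with Cochran-Mantel-Haenszel (CMH) by site, using 4,000 or more runs per setting.

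**Step 1: reproduce the stated level.** The only operating characteristic stated is 0.05. With the same infection rate at every site, or the same helmet use at every site, the pooled test rejects a true null in 4.6% to 5.4% of runs. The level holds in that case.

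**Step 2: null case with site differences, by formula.** Infection runs 10-40% and helmet use 20-80%, rising together, with no effect within any site.

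- Variance of eight equally spaced points on 0 to 1: (64 − 1)/12/49 = 0.1071.
- Between-site covariance of infection and helmet use: 0.30 × 0.60 × 0.1071 = 0.0193.
- Pooled risk if exposed: 0.25 + 0.0193/0.5 = 0.289. If unexposed: 0.25 − 0.0193/0.5 = 0.211.
- Spurious pooled odds ratio: (0.2886/0.7114)/(0.2114/0.7886) = 1.51.
- Noncentrality λ = N × 0.01929²/(0.25 × 0.75 × 0.5 × 0.5) = 0.00793 N, which is 1.59, 3.17 and 6.35.
- Rejection rate = Φ(√λ − 1.96) + Φ(−√λ − 1.96) = 24%, 43% and 71%.

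Simulation agrees: 24-25%, 42-44% and 71-72%. CMH stays at about 5%.

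**Step 3: vary the assumptions (null true).**

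| Infection by site | Helmet use by site | Relation | Pooled rejection at 25 / 50 / 100 per site |
|---|---|---|---|
| 10-40% | 20-80% | opposite | 24 / 44 / 73% |
| 10-40% | 20-80% | unrelated | 7 / 10 / 16% |
| 10-40% | 40-60% | together | 8 / 9 / 13% |
| 20-30% | 20-80% | together | 7 / 10 / 14% |
| 20-30% | 40-60% | together | 5-6% |

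CMH lies between 4.2% and 5.7% throughout.

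**Step 4: add the regression step (null true, Step 2 rates).** Suppose site is a candidate and is adjusted for whenever it passes the screen. Final false positives for helmet use fall to about 8%, 3-4% and 3% at 25, 50 and 100 per site. At 25 per site, site itself fails the screen in a little over a third of runs. At 50 it passes in about 95%.

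**Step 5: masked effect.** Within-site odds ratio 2; infection in unexposed workers 10-40%; helmet use 80% down to 20% as infection rises. The pooled risks become 0.340 exposed and 0.289 unexposed, an odds ratio of (0.340/0.660)/(0.289/0.711) = 1.27. Helmet use passes the pooled screen in about 11-12%, 20% and 36% of runs at 25, 50 and 100 per site. At 50 per site CMH detects it in 81-82%. Site passes the screen in about 80% of these runs at 50 per site, but that does not help, because helmet use has already been dropped.

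**The case against.** The strongest reply is that the screen is not the final analysis. The regression supplies the reported associations, and large site differences are just what would make site pass the screen. Step 4 bears this out: where site is a candidate, false positives are mostly corrected. The monthly forms ("they will complete monthly encounter forms to assess community and healthcare-related exposures") may also capture part of the local epidemic. This stands for false positives. It depends on site being a candidate, which the article neither states nor excludes, and it does not answer Step 5.

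A reader might infer that site confounding is certain here, or that the reported helmet result carries a false-positive rate of 25-71%. The documents support neither. Selection for geographic spread and patient volume makes site differences plausible, but the article gives no infection or helmet-use rates by centre, and kits go to all eight. The 25-71% describes the screen alone, under assumed rates.

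It can also be said that a condensed article leaves covariates to a fuller plan. That is fair for a covariate list. Here, though, the article does fix a rule, unadjusted significance as the condition of entry, and that rule is open to comment.

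**Conclusion.** The concern holds conditionally. As written, the screen names no site stratum and the regression has no forced site term. If infection and helmet use both vary materially between centres, the screen's 5% level is not maintained: about 25% to 71% over 25-100 workers per site in the wide, aligned case, 7-16% when the two are unrelated across sites, and 5-6% when both spreads are small.

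The firmer part is the loss of a real effect, because no later step in the stated plan can restore it: about 20% retention against about 82% with stratification, at 50 workers per site and a within-site odds ratio of 2. That figure needs helmet use to run opposite to infection across centres, which is an assumption. The direction and size of any bias in this study cannot be known from the article.

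**What to change.** Compare exposures between cases and controls with a site-stratified test (Cochran-Mantel-Haenszel). Enter helmet exposure and site in the logistic model whatever the screen shows, or use conditional logistic regression by site. Selection can still be used for the other risk factors.

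The cost is small but not nil. Seven degrees of freedom go to site. Precision falls if helmet use varies mainly between centres, since only the within-centre contrast is then used. In the prospective part, follow-up is at most six months and ends early if vaccine arrives, so cases may be few, and a centre without cases would contribute nothing to a stratified or conditional analysis. No new data are needed, because each worker's centre is known.

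### The prospective part of Aim 4b is analysed without time at risk or timing of exposure, which can give false helmet associations when there is no effect

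*Protocol article*

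**What the plan says.** The section on specific aim 4b describes two parts. The retrospective part uses everyone tested at time 0. Those without antibodies enter a prospective part: "They will be followed for up to 6 months during which they will complete monthly encounter forms". The purpose of the forms is given as "monthly encounter forms to assess community and healthcare-related exposures", together with recording PCR-confirmed diagnoses. Follow-up may end early: "the study will be censored and exit interview" and a second antibody sample are to be obtained "if and when COVID-19 vaccine becomes available at the designated COVID-19 treatment centers".

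Outcome status is defined as follows: "In the prospective study, a case is defined by seropositivity to SARS-CoV-2-specific antibodies, or a clinical case of SARS-CoV-2 infection confirmed by PCR testing", while "a control is defined by the absence of infection" by either test. Nothing ties a control to being at risk when a given case occurred.

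The Quantitative data analysis section gives one method for both the retrospective and the nested prospective study: "compare differences in exposures and risk factors observed between cases and controls using Chi-square" or Fisher's exact test, two-sided at 0.05, with significant variables passed to forward logistic regression. It mentions no person-time, survival model, time-varying exposure, matching or conditional analysis.

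**The concern.** The prospective part has the structure of a cohort: workers enter uninfected, exposure is recorded repeatedly, infections arise along the way, and follow-up can differ in length. A case-versus-control comparison that ignores time has two weaknesses here.

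- If a case's exposure is counted only up to infection, cases have had fewer months in which to become exposed than controls. The helmet then looks protective.
- If all follow-up is counted and its length differs widely between workers, those followed longer have had more chance of both exposure and infection. The helmet then looks harmful. Exposure after a PCR diagnosis is also credited to an infection that preceded it.

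Aim 4b asks whether helmet use alters healthcare workers' risk of infection. Of its two parts, this one can place exposure before infection. An artefact in the protective direction would be false reassurance on a safety question, in a study whose Discussion offers the findings as pilot data for scale-up elsewhere.

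**Working it through.** The article gives no sample size, infection rate or exposure prevalence for Aim 4b, so there is no figure of its own to reproduce. The check asks what the planned comparison would return with no helmet effect.

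**Inputs.** From the article: at most 6 months of follow-up, monthly exposure records, a time-ignoring comparison. Assumed: monthly exposure probability p = 0.15, independent from month to month; monthly infection risk h = 0.03; exposure coded as ever versus never.

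**Probability of being ever exposed by month k:** P(k) = 1 − 0.85^k. For k = 1 to 6: 0.150, 0.278, 0.386, 0.478, 0.556, 0.623.

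**A. Exposure counted to infection, 6 months for all.**
- Controls: P(6) = 0.623.
- Cases: average of P(k) over the month of infection, with weights 0.03 × 0.97^(k−1) rescaled to sum to 1 (0.180, 0.174, 0.169, 0.164, 0.159, 0.154). Result 0.403.
- Odds ratio = (0.403/0.597) / (0.623/0.377) = 0.41.
- If only half the cases have a PCR date and the rest are counted over all 6 months: cases (0.403 + 0.623)/2 = 0.513; odds ratio 0.64.
- Range: with p from 0.05 to 0.30 and h from 0.01 to 0.05, the odds ratio runs from 0.53 down to 0.24, always below 1.

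**B. All follow-up counted, half the workers stopped at s months and half at 6.** Risk of infection by month s is c(s) = 1 − 0.97^s, so c(2) = 0.0591 and c(6) = 0.1670. For s = 2:
- Cases: (0.0591 × 0.2775 + 0.1670 × 0.6229) / (0.0591 + 0.1670) = 0.533.
- Controls: (0.9409 × 0.2775 + 0.8330 × 0.6229) / (0.9409 + 0.8330) = 0.440.
- Odds ratio 1.45.

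By the same formula:

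| Shorter follow-up, s (months) | Null odds ratio |
|---|---|
| 1 | 2.10 |
| 2 | 1.45 |
| 3 | 1.19 |
| 4 | 1.07 |
| 5 | 1.01 |

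**C. Both mechanisms together.** Exposure stopped at infection and follow-up split: 0.70 for 2 versus 6 months, 0.98 for 1 versus 6. The two biases partly offset.

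**D. Simulation under no effect.** Assumed 400 workers at eight sites, 3% monthly infection, 20% monthly exposure, 1000 runs, uncorrected chi-square at two-sided 0.05:

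| Exposure coding | Follow-up | False positives | Median odds ratio |
|---|---|---|---|
| Ever, to infection or end | 6 months for all | 96.9% | 0.35 |
| Ever, to infection or end | Site stops at 4–6 months | 84.4% | 0.43 |
| Ever, to infection or end | Site stops at 1–6 months | 27.8% | 0.66 |
| Ever, all follow-up | 6 months for all | 4.9% | 1.00 |
| Ever, all follow-up | Site stops at 4–6 months | 4.5% | 1.04 |
| Ever, all follow-up | Site stops at 1–6 months | 18.8% | 1.40 |
| Fixed per worker | All three patterns | 4.0–5.6% | about 1.0 |
| Last month only | All three patterns | 4.2–5.1% | about 1.0 |

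The result also depends on how persistent exposure is within a worker. For ever exposed to infection or end, with 6 months for all, false positives are 6.1% if exposure is almost fixed per worker, 23.5% at an intermediate level and 72.6% if it varies mostly month to month.

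A month-by-month log-rank (Mantel-Haenszel) analysis with time-varying exposure gave 3.3–6.3% false positives and median odds ratios of 0.94–1.02 in every main setting, including runs with 200 and 800 workers.

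**The case against.** A reader might infer that the planned analysis must give false associations. The article does not support that. It does not say how the monthly forms become one exposure variable or whether a case's exposure window closes at infection, and an article may leave such derivations to a fuller document. Under some reasonable codings the chi-square test keeps its error rate near 5%. Monthly recording does not show that helmet exposure changes monthly. This part of the objection stands.

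A reader might also infer that workers are censored site by site as vaccine reaches each center. The wording speaks of the study being censored and of the centers in the plural, so a single stop is an equally fair reading. Staggered entry could still make follow-up unequal, but nothing in the article indicates a spread as wide as 2 versus 6 months, and with a narrow spread mechanism B nearly vanishes. This also stands. The figures 0.41 and 1.45 come from different scenarios and should not be read as two results of one analysis.

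Finally, the study is called nested, and logistic regression is a usual analysis for a nested case-control study. That would answer the concern if controls were drawn from those at risk when each case occurred and the analysis respected the matching. The article defines controls only by absence of infection and describes neither step.

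What remains is more than an omission. The article names a method, and that method leaves out the timing its own design collects. Mechanism A needs no assumption about vaccine dates.

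**Conclusion.** The concern holds as a statement of what can happen. The stated prospective analysis ignores time at risk and the order of exposure and infection, and can show an association when the helmet has none. With exposure that varies month to month and is coded as ever exposed up to infection, the null odds ratio is about 0.41 (0.64 if half the cases are undated). With all follow-up counted and widely differing stop times it exceeds 1: 1.45 for 2 versus 6 months, but only 1.01 to 1.07 for 5 or 4 versus 6. With exposure fixed per worker or read from a comparable recent window, there is little bias. Every magnitude rests on assumed exposure and infection rates, follow-up splits and, in the simulation, sample size. Neither the size nor the direction of bias in the actual study can be read from the article.

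**What to change.** In Quantitative data analysis, keep the present method for the retrospective part only and state a separate one for the prospective part:

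- Analyse person-months by pooled logistic or complementary log-log regression, or use a Cox model with time-varying exposure. Alternatively, sample controls from the risk set at each case's date and use conditional logistic regression.
- Count only helmet exposure recorded before the first positive test.
- Censor at exit (including vaccine-triggered exit), loss to follow-up or month 6.
- Treat infections found only by serology as interval-censored between the two samples, or compare them with workers of the same follow-up length.
- Adjust for site and calendar time as far as the number of cases allows.
- Confirm that the monthly form records helmet exposure; the article mentions community and healthcare exposures without naming it.

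The cost is mainly a change of analysis wording and slightly more complex modelling. Serology-only cases have no infection date, so their handling needs timing assumptions that should be stated in advance. If the form lacks a helmet item, one must be added.

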## Abstract

**Background:**

Acute respiratory failure, a major cause of death in COVID-19, is managed with high-flow oxygen therapy via invasive mechanical ventilation. In resource-limited settings like Nigeria, the shortage of ventilators and oxygen supply makes this option challenging. Evidence-based non-invasive alternatives to mechanical ventilation such as the use of continuous positive airway pressure (CPAP) devices exist, but there have been concerns that non-invasive ventilation may expose healthcare workers to infection from aerosolized dispersion of SARS-CoV-2. We propose to evaluate the feasibility, adaptability and acceptability of a CPAP/O_2_ helmet solution for non-invasive ventilation among patients with COVID-19 and health workers in eight COVID-19 treatment and isolation centers in Nigeria.

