### Study aims

1: Convene a Steering Committee of key stakeholders and recruit implementation sites to provide oversight for the development of processes for communication, decision-making, coordination, and distribution of CPAP/O_2_ helmet solutions for non-invasive ventilation at the eight COVID-19 treatment and isolation centers.

2: Use the integrated Promoting Action on Research Implementation in Health Services (i-PARiHS) framework to guide needs assessment, perform stakeholder analysis of the treatment centers’ capacity to use high-flow oxygen therapy to treat COVID-19 patients, and use the findings to develop a context-specific, practice facilitation strategy to implement the CPAP/O_2_ helmet solution for non-invasive ventilation.

3: Build infrastructure to support training and data monitoring processes and develop implementation protocols to evaluate the adaptability of the strategy for implementing use of CPAP/O_2_ helmets for non-invasive ventilation.

4: (a) Train healthcare workers; distribute a CPAP/O_2_ helmet solution for non-invasive ventilation, pilot test the practice facilitation [implementation] strategy, and assess feasibility of its use and acceptability; (b) estimate the altered risk of SARS-CoV-2 infection among healthcare workers associated with the use of CPAP/O_2_ helmets for non-invasive ventilation.

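### Aim 4b: helmet exposure gets an adjusted estimate only if it is significant, so a non-significant result could not answer whether staff infection risk is greater

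*Protocol article*

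**What the plan says.** The abstract gives the motive for aim 4b: "there have been concerns that non-invasive ventilation may expose healthcare workers to infection from aerosolized dispersion of SARS-CoV-2". The section on specific aim 4b is headed by a question in one direction, "Is the use of the CPAP/oxygen helmet associated with a greater risk of COVID-19 infection among healthcare workers", although its text postulates the opposite: "helmet ventilation may be associated with less risk of transmission of respiratory pathogens via aerosolization". The Study aims section words the same aim as estimation without a direction: "estimate the altered risk of SARS-CoV-2 infection among healthcare workers associated with the use of CPAP/O_2_ helmets for non-invasive ventilation".

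The section Quantitative data analysis covers both the retrospective and the nested prospective study. Cases and controls are compared on exposures and risk factors by chi-square or Fisher's exact test, and "All tests will use 2-tailed probability, with *P* values < 0.05 considered statistically significant". Variables that reach significance then go into a forward logistic regression, which is to supply the adjusted associations. Helmet exposure is not singled out from the other exposures in that section.

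**The concern.** A test of no difference can support greater risk or less risk. It cannot support a statement that risk is not greater, because P above 0.05 arises both when there is no effect and when there is a real effect and too few infections to show it.

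The entry rule adds to this. The adjusted estimate for the exposure that aim 4b is about exists only when the crude comparison is significant. In the case where a reader would most want to know how large an increase remains possible, the plan as written guarantees a non-significant P value and no adjusted estimate. That does not deliver the estimate promised in the aims, and it does not answer the question in the aim 4b heading. At stake is what can be said about the safety of staff who care for patients in helmets.

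**Working it through.** **No figure to reproduce.** The article gives no number of workers, infection proportion, helmet-exposed share, effect size or power for aim 4b. From the article: two-sided alpha 0.05, eight sites, prospective follow-up of up to 6 months, stopped early if vaccine reaches the centres. Everything else below is an assumption.

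**Step 1. What the rule yields under no effect.** If helmet exposure has no crude association with infection, a test at 0.05 is significant in about 5% of studies. An adjusted helmet estimate would therefore be produced in about 5% of such studies and be absent in about 95%.

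**Step 2. Chance of missing a real increase.** Assume N staff, a share e exposed, infection proportion p0 in the unexposed and odds ratio OR.

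p1 = OR·p0/(1−p0) / [1 + OR·p0/(1−p0)]

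Power = Φ{[(p1−p0) − 1.96·√(p̄(1−p̄)(1/n0+1/n1))] / √(p0(1−p0)/n0 + p1(1−p1)/n1)}

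Worked case: N = 400, e = 0.5, p0 = 0.10, OR = 1.5.
- p1 = 0.1429 and p̄ = 0.1214.
- Numerator: 0.0429 − 1.96 × 0.0327 = −0.0212. Denominator: 0.0326.
- Φ(−0.65) = 0.258, so the miss chance is 74%.
- Simulation of the same case (4000 runs) gave power of 27% for chi-square and 23% for Fisher.

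Miss chance (%), half of staff exposed:

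| OR | p0 | N=200 | N=400 | N=800 | N=1600 |
|---|---|---|---|---|---|
| 1.5 | 5% | 90 | 84 | 73 | 51 |
| 1.5 | 10% | 85 | 74 | 54 | 25 |
| 1.5 | 20% | 77 | 60 | 32 | 7 |
| 1.5 | 40% | 71 | 48 | 19 | 2 |
| 2.0 | 5% | 77 | 59 | 31 | 6 |
| 2.0 | 10% | 62 | 35 | 9 | 0 |
| 2.0 | 20% | 43 | 14 | 1 | 0 |
| 2.0 | 40% | 32 | 7 | 0 | 0 |

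With 30% exposed the figures move by a few points (OR 1.5, p0 10%, N = 800: 58% instead of 54%).

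**Step 3. What a flat result leaves open.** If the observed OR is exactly 1, the upper 95% limit is

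exp{1.96·√([1/e + 1/(1−e)] / [N·p(1−p)])}

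For N = 400, p = 0.10, e = 0.5: √(4/36) = 0.333, and exp(0.653) = 1.92. Over p from 5% to 40% with e = 0.5, the limit runs from 3.57 down to 1.76 at N = 200, from 2.46 to 1.49 at N = 400, from 1.89 to 1.33 at N = 800, and from 1.57 to 1.22 at N = 1600. These are crude limits; adjusted ones will usually be wider.

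P is 1 in every one of these settings, yet the increase in odds not excluded ranges from 22% to 257%. The interval separates these cases and the P value does not.

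**The case against.** The strongest reply is that the article never commits the faulty inference. It says which P values count as significant; nowhere does it say that a P value above 0.05 will be read as safe. A reader might infer from the aim 4b heading that non-significance is to be taken as reassurance, but no sentence states this. The aims list speaks of estimating an altered risk, and for an aim without a direction a two-sided test is not wrong. The postulate is of less risk, which the same test could support. All of this stands.

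It is also fair that sample size, interval reporting and rules of interpretation are commonly left to a full protocol or analysis plan, and neither is shown. Their absence from a journal article is not the point here. Nor is a non-inferiority margin obligatory in an observational part of a feasibility pilot.

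What the reply does not reach is the entry rule. That is stated, not omitted: the regression that is to give the adjusted associations admits only significant variables, with no exception for helmet exposure. This conflicts with the promise to estimate its effect, whatever a fuller document may add about intervals.

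**Conclusion.** The point holds in a limited form. As written, a non-significant helmet result leaves aim 4b without an adjusted estimate, and the P value alone cannot support a conclusion of no greater risk. This follows from the text and needs no assumption about sample size.

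The size of the risk does need assumptions. One might conclude that the test would often miss a real harm, but the article does not support that. Over the settings tabulated, the miss chance runs from about 0 to 90%: high with a few hundred staff and uncommon infection, low with 800 to 1600 staff and common infection. The supportable statement is that the rule could miss a real increase. Early stopping of follow-up on vaccine availability would reduce events in the prospective study, by an unknown amount.

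One might also infer that wider roll-out hangs on a reassuring aim 4b result. The Discussion ties scale-up to successful implementation in general and does not name this result. The change is worth making because it is a better way to answer the stated question at almost no cost.

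**What to change.** In Quantitative data analysis, for both the retrospective and the prospective study, add wording such as:

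*Helmet exposure is the main exposure for aim 4b. It will be kept in the adjusted logistic model regardless of its univariate P value and will not be subject to forward selection. Its adjusted odds ratio will be reported with a two-sided 95% confidence interval, and aim 4b will be answered from that interval. A lower limit above 1 indicates greater risk. Otherwise the upper limit will be stated as the largest increase in odds not excluded (an upper limit below 1 indicates lower risk). A non-significant P value will not be reported as evidence of no added risk.*

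The estimate must be the adjusted one: a crude upper limit could itself reassure falsely, given the community and workplace exposures that the study records.

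A margin is needed only if the investigators wish to claim no important increase; it should then be fixed before the data are examined. For scale, with a true OR of 1, half of staff exposed and 80% power, the number needed is (1.96 + 0.84)²·4 / [p(1−p)·(ln margin)²]. At infection proportions of 5, 10, 20 and 40%, that is about 1376, 727, 409 and 273 staff for a margin of 2.0, and 4021, 2122, 1194 and 796 for a margin of 1.5.

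The cost is analysis wording, with no extra staff, tests or visits. The downside is that the result may have to be reported as inconclusive.
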